**Fig. 1 Fig1:**
[figure not shown]
Standard Protocol Items: Recommendations for Interventional Trials (SPIRIT) Figure. Summary of data collection visits. *Performed at two centers (Umeå and Quebec) at a separate third visit during baseline and follow-up assessments. *NLPRT* non-linear periodized resistance training, *RT* resistance training, *ISWT* Incremental Shuttle Walk Test, *ESWT* Endurance Shuttle Walk Test, *UULEX* Unsupported Upper Limb Exercise Test, *60STS* 60-s Sit to Stand Test, *HRQoL* health-related quality of life

**Fig. 2 Fig2:**
[figure not shown]
Participant flow diagram

### Participants

A total of 64 patients (16 per center) aged between 40 and 89 years with stable moderate to very severe COPD (i.e., post-bronchodilator FEV_1_ < 80% of predicted), will be included.

Exclusion criteria consist of: patients with asthma as primary diagnosis, cardiovascular, neuromuscular, and/or skeletal diseases that are unstable and/or that may contribute to exercise limitation or any other contraindication to exercise; currently participating in a structured exercise or pulmonary rehabilitation program or been involved in pulmonary rehabilitation in the past 6 months; experienced a COPD exacerbation and/or change in medication dosage/frequency in the past 6 weeks. Participants are prohibited to participate in other organized training programs during the trial period but are encouraged to continue with normal everyday physical activity.

### Procedure

Before commencing outcome assessment, all procedures will be explained and the informed consent form will be reviewed and signed. Participants will perform two test visits (three if accepting a muscle biopsy) before the start of the study and immediately following the 8-week intervention period, with adequate recovery between tests and test visits. The same tests and procedures will be used across centers, and pre- and post-intervention assessments will be performed in the same time of the day, with strictly standardized procedures. A summary of study visits and participant data collection schedule are presented in Fig. 1 (SPIRIT Figure), and the flow diagram for the overall study in Fig. 2. Screening and enrollment are planned to start in the spring of 2018 and continue until the target sample size is reached. A 2-year recruitment period is expected. The site investigator at each center will be responsible for the enrollment of participants.

### Sample size calculation

Multicenter trials involve a correlation in data, i.e., participants from the same center are likely to be more similar than subjects from other centers. As such, a correlation potentially affects the statistical power of the trial the sample size needs to be adjusted, often increased, to account for the design of the study [21]. To minimize the effect of using different centers, eligibility criteria as well as design and delivery of training interventions are standardized across centers. Furthermore, in an individually randomized trial that is stratified for centers, similar to the present trial, the design effect is estimated to be < 1 which involves a gain in power, allowing a reduction in sample size rather than an increase [21, 22]. Nevertheless, the sample size calculation is performed with a design effect of 1 and is based on the results from a resistance training meta-analysis on healthy adults in which a group difference of 1.16 (SD 1.09) was seen on muscle function when comparing NLPRT with RT [18]. Thus, based on an expected group difference in effect size of 1.16 (SD 1.09) on muscle function with a power of 80%, two-sided alpha of 0.05 (including 15% drop-outs) 16 patients per group is required (32 in total). However, we plan to recruit a total of 64 patients with an equal distribution of men and women. The planned sample size (*n* = 64, including 15% drop-out) will be sufficient to have power for subgroup analysis based on sex (male and female).

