### Randomization and masking

A person not involved with either enrollment, assessments nor training of participants will generate the allocation sequence and assign participants to one of the two interventions.

To prevent foreknowledge of treatment assignment and to keep the allocation sequence concealed from the participants and the researchers, group allocation will be done after the completion of baseline and inclusion tests with a computer random-number generator. Individual randomization, stratified for centers and sex, will be performed with a 1:1 allocation to the intervention and control groups. The allocation sequence will be kept in an opaque, sealed and stapled envelope and will be kept concealed until the end of the outcome assessment. The envelope will be made impermeable to intense light by using aluminum foil inside and sealed using tamper-proof labels.

The outcome assessors will be masked to group allocation. Furthermore, the participants will be given repeated instructions not to reveal their group allocation to the outcome assessors. In case of failure in keeping the outcome assessor masked (i.e., a patient reveals their group allocation), a second trained outcome assessor will be available.

Due to the nature of the intervention neither participants nor instructors of the training sessions will be masked during the intervention, the hypotheses of the trial will, however, not be revealed to the participants before and during the trial. The data analysts will be masked to group allocation.

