### Statistics

The primary analyses will be an intention-to-treat analysis (including all participants randomized) in addition, a complete case population (participants with complete outcome measurements independent on adherence to intervention), and a per-protocol analysis (defined as at least 80% overall attendance rate as well as no exacerbations during the last 2 weeks prior to follow-up assessment) will be performed. Missing data will be imputed in the intention-to-treat analysis using multiple imputation assuming data is missing at random conditional on participant severity of disease and history of exacerbations. This is because severity of disease and history of exacerbations are known risk factors for future exacerbations and may affect adherence to the training protocol [28].

Mixed models will be used for analysis of data with individuals at level 1 and center at level 2. Estimates of effect sizes will be computed using Cohen’s *d* (*d* = difference in group means/error SD within). Calculated as the difference between predicted means from the final mixed-effects model for a given pair of groups divided by the estimated within-group error SD in the model with the estimated value of $$ 2{\sigma}_e^2 $$, where $$ {\sigma}_e^2 $$ is the residual variance. To judge the quality of the model we will analyze the residuals. For responsiveness, values of 0.20, 0.50 and ≥ 0.80 correspond to small, moderate and large responsiveness, respectively [50].

We will consider two-sided *p* values < 0.05 as statistically significant for the primary outcomes without correction for a multiplicity of tests assuming that each test represents an independent function based on the specificity principle of training [26]. Relationships between parameters will be evaluated using Pearson correlation coefficients. The strength of the correlation coefficients will be categorized as low (0–0.25), moderate (> 0.25–0.50), strong (> 0.50–0.75), very strong (> 0.75). Pre-planned subgroup analyses are differences between men and women. Statistical analysis will be performed using the statistical package SPSS 23.1.

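### Training is delivered in small groups, but the sample size and the stated model allow only for center correlation, so a design effect of 1 is not necessarily cautious

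*Protocol article*

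**What the plan says.** - **Sample size calculation.** The one source of correlation discussed is center: "participants from the same center are likely to be more similar than subjects from other centers". For an individually randomized, center-stratified trial the article states that "the design effect is estimated to be < 1 which involves a gain in power, allowing a reduction in sample size rather than an increase". It then adds that "the sample size calculation is performed with a design effect of 1", which reads as the cautious choice.
- **Randomization and masking.** "Individual randomization, stratified for centers and sex, will be performed with a 1:1 allocation to the intervention and control groups".
- **Training interventions.** Among the features common to both arms, all sessions are supervised by local staff in a group format of roughly two to four participants, three times a week for 8 weeks. The article does not say whether a group holds one arm or both, or whether membership stays fixed.
- **Statistics.** "Mixed models will be used for analysis of data with individuals at level 1 and center at level 2". No level or term for training group is named. The article chose these levels itself, so this is a stated analysis choice and not a detail left open.

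**The concern.** The center argument works because both arms are present in every center, so center differences cancel from the treatment contrast. That reasoning does not carry over to groups formed after randomization. If such a group follows one program, anything its members share (coaching, encouragement, pace, company) is nested within arm and does not cancel, even though allocation was individual.

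Single-arm groups are plausible, because the two programs differ in sets, repetitions, rest and progression rules. The primary outcomes, 1RM and repetitions to failure, depend on effort and so could respond to shared coaching. If correlation of this kind exists and the model omits it, confidence intervals are too narrow and the 0.05 tests reject too often. Each primary outcome is tested at 0.05 without multiplicity correction, so this would affect each of those tests.

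**Working it through.** **Inputs from the article.** Difference 1.16 with SD 1.09, so d = 1.16/1.09 = 1.064; power 80%; two-sided alpha 0.05; drop-out 15%; 16 per group required; 64 planned, 16 per center; about 2-year recruitment; 8 weeks of training; group size m of about 2 to 4.

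**Assumptions, not in the article.** Training-group ICC of 0.01 to 0.10; where used, a center ICC of 0.10.

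**1. The plan's own figure.** n per arm = 2 × ((1.960 + 0.842)/1.064)² = 13.86. Multiplying by 1.15 gives 15.9 and dividing by 0.85 gives 16.3. The stated 16 per group is reproduced at a design effect (DE) of 1.

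**2. Single-arm groups.** DE = 1 + (m − 1) × ICC. A test that ignores the grouping has actual two-sided error 2 × (1 − Φ(1.96/√DE)). Power is from the noncentral t at 27.2/DE per arm, where 27.2 = 32 × 0.85.

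| m | ICC | DE | Actual error | Power at 64 |
|---|---|---|---|---|
| 2 | 0.01 | 1.01 | 0.051 | 97% |
| 2 | 0.05 | 1.05 | 0.056 | 96% |
| 2 | 0.10 | 1.10 | 0.062 | 96% |
| 3 | 0.05 | 1.10 | 0.062 | 96% |
| 3 | 0.10 | 1.20 | 0.074 | 94% |
| 4 | 0.01 | 1.03 | 0.053 | 97% |
| 4 | 0.05 | 1.15 | 0.068 | 95% |
| 4 | 0.10 | 1.30 | 0.086 | 92% |

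Overall power falls to 80% only at DE of about 27.2/13.86 = 1.96 (normal approximation).

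**3. Groups that mix arms equally.** The group effect now cancels from the contrast but stays in the residual variance. The variance ratio is 1 + (m/2 − 1) × ICC − (m/2) × ICC = 1 − ICC. At ICC 0.05 and 0.10 the actual error is 2 × (1 − Φ(1.96/√0.95)) = 0.044 and 2 × (1 − Φ(1.96/√0.90)) = 0.039, so the test is slightly conservative.

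**4. Does the center gain offset this?** For power it can: DE = 1 − ICC(center) + (m − 1) × ICC(group). With a center ICC of 0.10, DE exceeds 1 only if the group ICC is above 0.10 (m = 2), 0.05 (m = 3) or 0.033 (m = 4). For the error rate it does not, because a model that has removed center variance still treats grouped residuals as independent. The ratio becomes 1 + (m − 1) × ICC(group)/(1 − ICC(center)). For m = 4 and both ICCs 0.10 this is 1 + 0.3/0.9 = 1.33, giving an error of about 0.090. Simulating the planned layout (4 centers, 8 per arm per center, center adjusted for, no group term) gave 0.086 to 0.093 for m = 4 at group ICC 0.10, and 0.062 to 0.066 for m = 2.

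**5. How many same-arm companions are likely?** Under even accrual (an assumption), 16/104 × 8 = 1.2 trial participants are in training at a center at any time, both arms together. A participant then has on average 7/104 × 8 = 0.54 same-arm companions. Putting 0.54 in place of m − 1 gives a DE of 1.005 to 1.054 and an actual error of about 0.051 to 0.056.

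**The case against.** The case on the other side is substantial, and most of it limits the size of the point.

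- **The statement about center is not wrong.** It is confined to center-stratified individual randomization, and the same paragraph says that correlation often calls for a larger sample. This stands: the text is incomplete, not false.
- **Nothing says that groups are single-arm or stable.** This stands. A reader might infer that group delivery in itself pushes the design effect above 1. The article does not support that, since it depends on arm composition, stability and an ICC that are not given, and for power also on the offsetting center gain.
- **Staff may serve both arms, and progression is individual.** The first would place instructor effects largely at center level, and the second suggests a small ICC. Both are fair.
- **Slow accrual leaves few same-arm companions.** This stands unless enrolment is batched. Groups of two to four would otherwise need mixed arms or non-trial patients, and the article describes none of these.
- **Power is not threatened overall.** This stands at 64 patients. A reader might also blame clustering for weak power within each sex. About 13.6 evaluable per arm and sex (16 × 0.85) gives 76% by the t-test at a design effect of 1, so that shortfall exists before any clustering.
- **A group term is detail for the analysis plan.** Only in part. The article states the model's levels, and those levels leave out a feature of delivery that the article itself describes.

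**Conclusion.** The point holds conditionally. The sample size text and the stated model recognize center as the only source of correlation, although all training is given in small groups. A design effect of 1 is therefore not shown to be cautious, and the model's standard errors can be wrong in either direction: too small if groups are single-arm and stable, slightly too large if they mix arms.

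For single-arm groups and an assumed ICC of 0.01 to 0.10, the actual error rate is about 0.05 to 0.06 for groups of two and up to about 0.087 for groups of four, or about 0.09 if there is also a center ICC of 0.10. Expected accrual suggests the low end. Overall power at 64 stays at 92% or more over this range, so the reason to act is the calibration of tests and intervals, not the number of patients. This is a cheap improvement of minor priority.

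**What to change.** 1. In the sample size section, limit the statement that the design effect is below 1 to the center effect, and say that correlation within training groups was not allowed for.
2. Record the training group each participant mainly attended, and state whether groups hold one arm or both.
3. In the Statistics section, add a random effect for training group to the model for the primary outcomes. If its variance cannot be estimated, which is possible with such small groups, use cluster-robust standard errors by training group, with a small-sample correction, as a sensitivity analysis.

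The cost is one recorded variable, one model term or sensitivity analysis, and a simple rule for participants who change groups. Intervals become slightly wider if groups are single-arm. No extra patients are needed.

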### Trial registration

The clinical trial has been registered before the enrollment of the first participant. Date of trial registration: 13 April 2018. ClinicalTrials.gov identifier: NCT03518723. The recruitment will begin in 2018 and will continue until sufficient power is reached.

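### The power claimed for the sex subgroup analysis covers a treatment test within each sex, not the comparison of men with women that the Statistics section names, which has about 49% power at best-case size

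*Protocol article*

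**What the plan says.** The Sample size calculation section of the protocol article takes from a meta-analysis in healthy adults that "a group difference of 1.16 (SD 1.09) was seen on muscle function when comparing NLPRT with RT". From this it concludes that "with a power of 80%, two-sided alpha of 0.05 (including 15% drop-outs) 16 patients per group is required (32 in total"). It then plans 64 patients, half men and half women, and says this size "will be sufficient to have power for subgroup analysis based on sex (male and female"). It gives no effect size or power figure for the subgroup analysis.

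The Statistics section describes the subgroup analysis in one sentence: "Pre-planned subgroup analyses are differences between men and women". The Randomization and masking section stratifies the 1:1 allocation by center and sex, so each sex should split evenly between the arms.

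**The concern.** In a two-arm trial, a difference between men and women that bears on the intervention is a difference between two treatment effects, that is, a treatment-by-sex interaction. With equal cells, its standard error is twice that of the overall treatment effect. Doubling a sample that was sized for one treatment comparison gives each sex a full-size comparison of its own, but does not give comparable power for the contrast between the sexes.

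The sex subgroup is the only reason the section offers for going from 32 to 64. A reader who takes the power statement to cover the analysis named under Statistics could treat a non-significant sex contrast as good evidence that the training works alike in men and women. A trial of this size could not support that conclusion.

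**Working it through.** **Inputs.** All come from the protocol article.
- Difference 1.16, SD 1.09, 80% power, two-sided alpha 0.05, 15% drop-out, design effect 1 (Sample size calculation).
- 64 patients, half men and half women (same section); 1:1 allocation stratified by sex (Randomization and masking). This gives 16 randomized per sex-by-arm cell and 16 × 0.85 = 13.6 completers per cell.
- Assumed here: the same SD and drop-out in all four cells.
- Assumed here: the size of the interaction, since the protocol gives none. Two values are used: the whole planned effect (1.16, or 1.16/1.09 = 1.06 SD) and half of it (0.58).

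**1. The plan's own figure.** n per arm = 2 × [SD × (1.960 + 0.842)/difference]² = 2 × [1.09 × 2.802/1.16]² = 13.86. Allowing for drop-out, 13.86/0.85 = 16.3. The stated 16 per group reproduces to within rounding; rounding up first gives 14, then 17. A t-test needs 15 per arm, or 18 with drop-out.

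**2. Treatment comparison within one sex, 64 recruited.** SE = 1.09 × √(2/13.6) = 0.418. Then 1.16/0.418 = 2.775, and power = Φ(2.775 − 1.960) = 79%. The noncentral t gives 76%. This is close to the planned 80%.

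**3. Treatment-by-sex contrast, 64 recruited.** SE = 1.09 × √(4/13.6) = 0.591. For comparison, the overall treatment effect with 27.2 completers per arm has SE = 1.09 × √(2/27.2) = 0.296, half as large.

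| Interaction | Completers per cell | Power, normal | Power, t |
|---|---|---|---|
| 1.16 (whole planned effect) | 13.6 | 50.1% | 48.6% |
| 1.16 | 13 | 48.3% | 46.8% |
| 1.16 | 14 | 51.2% | 49.8% |
| 1.16 | 16 (no drop-out) | 56.7% | 55.3% |
| 0.58 (half) | 13.6 | 16.4% | 16.1% |

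First row by hand: 1.16/0.591 = 1.962, and Φ(1.962 − 1.960) = 50%.

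**4. What the contrast could detect.** At 80% power, 2.802 × 0.591 = 1.66, which is 1.66/1.16 = 1.43 times the whole planned effect.

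**5. Size needed for 80% power at 1.16.** Per cell, 4 × [1.09 × 2.802/1.16]² = 27.7, so 28 per cell or 112 completers. That is 112/0.85 = 131.8, about 132 recruited. The t-test needs 29 per cell, or 116 completers and about 137 recruited. This only shows the gap; enlarging the trial is not proposed.

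**The case against.** The strongest reply is that the sample size sentence, on its natural reading, makes no claim about an interaction. It sizes one comparison at 32, doubles it with equal numbers of men and women, and so provides one full comparison per sex. On that reading 64 is roughly right, as step 2 shows. This stands: a reader might infer that the sample size arithmetic is wrong, and it is not. The difficulty arises only when that section is set beside the Statistics section.

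The sentence under Statistics is also short. It names no interaction term, contrast or outcome, and the model may be left to a fuller document. That stands too, so the interaction reading is an interpretation, although it is the ordinary meaning of a difference between men and women in a two-arm trial. The 49% also depends on an interaction size chosen for this check. The choice is generous, since it corresponds, for example, to the full benefit in one sex and none in the other.

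Two stronger inferences are not supported:
- A reader might expect that significance in one sex only will be reported as a sex difference. No section proposes this. The fix guards against it, but it is not a fault in the text.
- A reader might infer from the Trial registration section, where recruitment "will continue until sufficient power is reached", that the end of recruitment is open. The Participants section and the Sample size calculation both fix 64, and the Procedure section says enrollment will "continue until the target sample size is reached". No interim look or power-based stopping rule appears anywhere, so the registration sentence is only a loose paraphrase.

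**Conclusion.** The point holds as a mismatch between two sections. The stated power fits separate treatment comparisons within each sex (about 76–79% each). It does not fit the analysis named under Statistics if that is a treatment-by-sex contrast: about 49% for an interaction equal to the whole planned effect, about 16% for half of it, and no more than 57% for the full size even with no drop-out. Rounding, drop-out and the choice of test do not change this.

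The figures rest on the protocol's SD of 1.09 in every cell, equal drop-out, a design effect of 1 and the assumed interaction sizes. Severity is moderate: this is a subgroup analysis, and the primary NLPRT-versus-RT comparison does not depend on it.

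**What to change.** In the Sample size calculation, limit the power statement to what 64 patients deliver, for example: with 64 randomized and 15% drop-out, the NLPRT-versus-RT comparison within each sex has about 76–79% power for a difference of 1.16 (SD 1.09); the comparison of treatment effects between men and women is exploratory, with about 49% power for an interaction of 1.06 SD.

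In the Statistics section, say that sex differences in the training effect will be assessed by an arm × sex term in the mixed model, reported with a 95% confidence interval, and that a sex difference will be claimed only from that term.

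The cost is a less favourable stated power and one additional model term. No extra patients are needed, and the primary analysis does not change.

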### Randomization and masking

A person not involved with either enrollment, assessments nor training of participants will generate the allocation sequence and assign participants to one of the two interventions.

To prevent foreknowledge of treatment assignment and to keep the allocation sequence concealed from the participants and the researchers, group allocation will be done after the completion of baseline and inclusion tests with a computer random-number generator. Individual randomization, stratified for centers and sex, will be performed with a 1:1 allocation to the intervention and control groups. The allocation sequence will be kept in an opaque, sealed and stapled envelope and will be kept concealed until the end of the outcome assessment. The envelope will be made impermeable to intense light by using aluminum foil inside and sealed using tamper-proof labels.

The outcome assessors will be masked to group allocation. Furthermore, the participants will be given repeated instructions not to reveal their group allocation to the outcome assessors. In case of failure in keeping the outcome assessor masked (i.e., a patient reveals their group allocation), a second trained outcome assessor will be available.

Due to the nature of the intervention neither participants nor instructors of the training sessions will be masked during the intervention, the hypotheses of the trial will, however, not be revealed to the participants before and during the trial. The data analysts will be masked to group allocation.

